##### Exploratory outcomes

The objective of these analyses are to explore differences in intervention effectiveness within and across racialized groups, ethnicity, and SDOH using the same outcomes as Aims 1. The standard approach to moderation using regression models that include a ‘treatment by race interaction’ variable has multiple pitfalls, including lack of consideration of within-group differences [89]. Thus, we will incorporate suggested alternatives less likely to lead to misleading findings [89–91]. These include examining the efficacy of a specific treatment within a racialized and/or ethnic minoritized group (e.g., is BNI + MAUD significantly more effective than BNI for Black individuals?) as well as evaluating the efficacy of a specific treatment across different racialized and/or ethnic groups (e.g., are there significant differences in AUD treatment engagement for BNI + MAUD between Black and White individuals?). These analyses will be conducted with similar statistical approaches as Aim 1 (i.e., logistic regression for engagement outcomes, random effects regression for change in alcohol use outcomes). Furthermore, it is important to consider why specific treatments might yield more favorable results within or between certain racialized or ethnic groups. Accordingly, and informed by the Socio-Ecological Model (Fig. 1), we will evaluate SDOH as key moderators of intervention effects on AUD treatment engagement and alcohol use post-discharge. In these models, logistic regression will be used to examine the effect of the interaction of multiple individual-level SDOH (for example employment, education, housing instability, food insecurity, transportation insecurity, medical mistrust, discrimination experiences) by treatment condition on AUD treatment engagement post-discharge. We will also examine individual-level SDOH as a latent variable in Structural Equation Models evaluating the impact as a moderator of treatment effectiveness on post-discharge engagement and alcohol use outcomes.

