
### Study aims and hypotheses

Among 450 hospitalized individuals with untreated moderate to severe AUD (by Diagnostic and Statistical Manual-5 [DSM-5] criteria), our aims are to evaluate the effectiveness of hospital-initiated BNI vs. BNI + MAUD vs. BNI + MAUD + CBT4CBT on AUD treatment engagement at 34 days (primary outcome) and 90 days post-discharge; changes in alcohol use by self-report and biomarker over the 90 day period; and (exploratory) health care utilization, including Emergency Department visits and hospital readmission (Aim 1). We hypothesize that BNI + MAUD + CBT4CBT will be more effective than BNI + MAUD, which will be more effective than BNI alone as evidenced by higher rates of AUD treatment engagement, and reductions in alcohol use and urgent and emergency healthcare utilization post-discharge.

We will explore whether the effectiveness of the interventions on AUD treatment engagement and alcohol use outcomes differs across and within racial and ethnic groups and by SDOH indicators that reflect sequalae of structural racism (Aim 2). We hypothesize that there will be no difference in treatment effectiveness by race or ethnicity after adjustment of confounders but there will be differences based on SDOH.

Consistent with our prior experiences [40], we will additionally conduct an implementation-focused process evaluation [21], involving process measures, a clinician and staff survey, in addition to obtaining measures of the amounts and unit costs of resources used to implement each intervention to patients as well as health care staff. Analyses of cost, cost effectiveness, possible cost-savings benefits from reduced use of health care following the intervention, and cost–benefit for each intervention will compare individual-level provider and patient costs, indices of cost-effectiveness, and indices of cost–benefit for the three intervention combinations, as well as intervention-level indices of incremental cost-effectiveness ratios (ICERs) [41, 42] (Aim 3).

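### Aim 2 hypothesises no difference in treatment effectiveness by race or ethnicity, but neither analysis named for it estimates the between-group difference in treatment effect

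*Protocol article*

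**What the plan says.** The hypothesis is in the protocol article under Study aims and hypotheses: "We hypothesize that there will be no difference in treatment effectiveness by race or ethnicity after adjustment of confounders". This is a statement about effect modification, that is, whether the arm contrast is the same in each group.

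The method is under Statistical analyses, Exploratory outcomes. There the treatment-by-race interaction "variable has multiple pitfalls, including lack of consideration of within-group differences". The plan continues: "Thus, we will incorporate suggested alternatives less likely to lead to misleading findings". Two alternatives are named:

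- **(a) Within one group:** "examining the efficacy of a specific treatment within a racialized and/or ethnic minoritized group", with the example "is BNI + MAUD significantly more effective than BNI for Black individuals".
- **(b) Across groups:** "as well as evaluating the efficacy of a specific treatment across different racialized and/or ethnic groups", with the example "are there significant differences in AUD treatment engagement for BNI + MAUD between Black and White individuals".

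These are to use approaches similar to Aim 1, i.e. logistic regression for engagement. Interactions with treatment are planned for the social determinants of health (SDOH). No between-group contrast of treatment effects is named for race or ethnicity, and the confounder adjustment in the hypothesis is not described for (a) or (b).

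**The concern.** The hypothesis concerns a difference of differences: the effect of an arm over its comparator in one group, minus the same effect in another. Analysis (a) asks whether an effect is detectable in one group, and its answer depends heavily on how many participants that group has. Analysis (b) compares outcome levels in a single arm. With no comparator arm it cannot separate a different treatment effect from a different starting level, although the text labels it efficacy.

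At stake is the conclusion the section wants to avoid. A reader may take significance in a large group and non-significance in a smaller minoritized group as evidence that the intervention works in one and not the other, when the effect is the same in both. Nor does a non-significant comparison of either kind show that effectiveness is equal.

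**Working it through.** The section states no figure to reproduce, so the check asks how the two named analyses behave when the treatment effect is identical in every group.

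**Inputs**
- From Justification of sample size: base rate 40%; increase 15 points (to 55%); 150 per arm, or 120 per arm after 20% loss; alpha 0.025 for the two Aim 1 contrasts. No alpha is stated for Aim 2, so 0.05 and 0.025 are both used, two-sided.
- Group shares (assumption): the hospital's source population in Study context is 27% Black and 13% Hispanic or Latino. These are treated as non-overlapping, and the remaining 60% as one comparison group. No White share and no enrolled mix are given, so an assumed 35/25/40 mix is also run.

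**Analysis (a).** With n per arm in a group, power ≈ Φ(0.15/√(0.4875/n) − z), where 0.4875 = 0.40×0.60 + 0.55×0.45 and z is the two-sided critical value. For 150 per arm and 27/13/60, n = 40.5 (Black) and 90 (largest group). At alpha 0.05, power is 0.277 and 0.531.
- Largest group significant, Black not: 0.531 × (1 − 0.277) = 0.384.
- Discordant either way: 0.384 + 0.277 × (1 − 0.531) = 0.514.

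| Mix | Per arm | Alpha | Power, Black | Power, largest | Largest significant, Black not | Discordant |
|---|---|---|---|---|---|---|
| 27/13/60 | 150 | 0.05 | 28% | 53% | 38% | 51% |
| 27/13/60 | 150 | 0.025 | 19% | 42% | 34% | 45% |
| 27/13/60 | 120 | 0.05 | 23% | 45% | 34% | 47% |
| 27/13/60 | 120 | 0.025 | 15% | 34% | 29% | 39% |
| 35/25/40 | 150 | 0.05 | 34% | 38% | 25% | 46% |
| 35/25/40 | 150 | 0.025 | 25% | 28% | 21% | 39% |
| 35/25/40 | 120 | 0.05 | 29% | 32% | 23% | 42% |
| 35/25/40 | 120 | 0.025 | 20% | 23% | 18% | 33% |

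A simulation of 400,000 trials per scenario (Wald log-odds tests, hospital mix) agrees closely: discordance of 50% and 42% at 150 per arm, and 47% and 37% at 120 per arm, for alpha 0.05 and 0.025.

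**Analysis (b).** The odds ratio is the same in both groups: (0.55/0.45)/(0.40/0.60) = 1.83. Only the BNI base rates differ, and these gaps are assumptions. Simulated percentage of trials in which the BNI + MAUD arm alone shows a significant group difference, hospital mix:

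| Base rates, Black vs largest group | 150 per arm, 0.05 | 120 per arm, 0.05 | 120 per arm, 0.025 |
|---|---|---|---|
| 40% vs 40% | 4.4% | 4% | 2% |
| 35% vs 45% | 18% | 16% | 10% |
| 30% vs 45% | 38% | 32% | 22% |
| 30% vs 50% | 59% | 50% | 39% |

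Hand check for 35% vs 45%, 150 per arm, alpha 0.05: the odds ratio turns these into 49.7% and 60.0%. SE = √(0.25/40.5 + 0.24/90) = 0.094, so z = 0.103/0.094 = 1.10 and power is about 19%.

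**Treatment-by-group contrast.** In the same simulations it is falsely significant in 4.6–4.8% of trials at alpha 0.05 and 2.2–2.4% at 0.025, including where base rates differ. On the risk-difference scale its 95% half-width, Black vs the largest group, is 1.96 × √(0.4875/40.5 + 0.4875/90) = 0.259. With 120 per arm (32.4 and 72) it is 0.289. Power for an effect of 0 vs +15 points is about 21% at 150 per arm and alpha 0.05. The difference detectable with 80% power is about 37 points (about 41 at 120 per arm).

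**The case against.** The strongest defence has five parts.

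1. **Aim 2 is exploratory and the list is open.** The text introduces the alternatives as included examples, so an interaction contrast is not excluded. This stands, and it would be wrong to say that the plan forbids one. But the section argues against the interaction and names none for race or ethnicity. That is a stated choice, not a detail left to an analysis plan.
2. **Analysis (a) is a legitimate question with nominal error.** This also stands. The false difference arises only when discordant verdicts are read as effect modification, and no such reading rule is written. The plan's hypothesis invites that reading, because nothing else named addresses it.
3. **Analysis (b) inflates only if base engagement differs.** This is correct. The documents give no group-specific engagement rates. The Introduction says that treatment rates differ across racial and ethnic groups, which makes a gap plausible but does not size it. If the comparison were also run in the BNI arm, or adjusted, the base gap would become visible, but neither step is described for it.
4. **Interactions for SDOH but not for race look inconsistent.** A reader might infer this, but the documents do not support it. SDOH are presented as the explanatory moderators, and the stated objection is specific to treatment-by-race terms.
5. **The interaction is badly underpowered and cannot confirm no difference either.** This is true, and it is why the contrast should be an estimate with an interval and not another test verdict.

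**Conclusion.** The point holds as a mismatch between a stated hypothesis and the analyses named for it, whatever the enrolled group sizes turn out to be. The size does depend on assumptions. With an identical effect, within-group verdicts disagree in roughly 33–51% of trials, and the specific pattern of significance in the largest group but not in Black participants occurs in roughly 18–38%. The same-arm comparison is significant in roughly 10–59% of trials under assumed 10–20 point base gaps and the hospital mix, and keeps its nominal error with no gap.

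A reader might infer that the trial will probably report a benefit confined to the largest group. The figures do not support that: the pattern stays below 40% in every setting examined, and it misleads only if the verdicts are compared. The problem does not extend to the SDOH moderators or to the primary analysis.

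**What to change.** - Keep the within-group estimates, with 95% CIs and without significance verdicts.
- For each planned contrast, add the between-group difference in treatment effect with a 95% CI, adjusted for confounders as the hypothesis states. Name the scale: a ratio of odds ratios from the logistic model, or a difference of standardised risk differences. With unequal base rates the two scales can disagree on whether effects are equal.
- Describe same-arm comparisons between groups as engagement levels, not efficacy.
- State that a non-significant result does not establish the hypothesis "no difference in treatment effectiveness by race or ethnicity after adjustment of confounders", and give the expected half-width of about 26–29 points for Black participants vs the largest group.

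**Cost.** No new data are needed, and race and ethnicity is already a balancing factor in the urn randomization. The model needs at least (3 − 1) × (3 − 1) = 4 interaction terms for three arms and three groups, plus a standardisation step if risk differences are chosen. The downside is that the contrasts will be visibly imprecise.

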#### Implementation-focused process evaluation

Informed by work of others [21] and our own experiences [40, 92], we will conduct an implementation-focused process evaluation to gain an understanding of the necessary factors for building the infrastructure for this clinical trial, delivering the associated interventions in the hospital setting, and then potentially sustaining the interventions outside the context of a funded study. We will ground our evaluation in RE-AIM (Reach, Effectiveness, Adoption, Implementation, Maintenance) with particular attention to promoting health equity [93–95]. To achieve these goals, data sources complementing participant assessments will include screening and enrollment logs (e.g., reasons patients decline study participation); recordings from intervention sessions; minutes from study team meetings; time, transportation, and other resources that participants as well as the HPAs and other healthcare staff contribute to interventions; as well as patient satisfaction data collected as part of the follow-up assessments.

Intervention-level cost per engaged patient will be calculated, along with increments in this cost as successive interventions are added. We will conduct analyses to determine the type, amount, and monetary values (i.e., costs) of the major resources used to implement each intervention for each patient, including time of professionals and patients, medication, and other intervention materials and resources. Combining cost with effectiveness data for individual patients will make possible descriptive scattergrams and group-level graphs of effectiveness = *f* [costs] and benefits = *f*[costs] as well as statistical analyses comparing effectiveness/cost ratios (e.g., change in PHDD per $100 of resources consumed by intervention) and other indices of relationships between costs and effectiveness for patients in each intervention condition. Average and median effectiveness/cost will be compared statistically for each condition with individual-level effectiveness and costs [58]. Cost per effectively treated patient also will be calculated at the group level, defining effective treatment according to quantitative definitions of clinically meaningful change in alcohol use. Similar analyses will examine graphically and statistically cost–benefit relationships as expressed by individual-level net benefit (i.e., reduction following intervention in costs of ED and readmission minus costs of intervention) [58]. Further, building on a mixed-methods evaluation that informed the study protocol [44], we will conduct a survey of hospital-based clinicians and staff upon conclusion of the clinical trial regarding their perspectives on the alcohol treatment interventions and necessary supports to sustain delivery of these interventions outside of the research infrastructure. We will also capture factors that may contribute to inequitable care among historically minoritized racial and ethnic groups.

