### Intervention components overview

#### Brief negotiation interview with telephone booster (BNI)

All participants receive the BNI with referral to aftercare AUD treatment and opportunity for a 2-week telephone booster delivered by a dedicated trained Health Promotion Advocate (HPA). The BNI contains the essential components of effective brief interventions [59–64] and includes training materials that have been used to train non-specialists in various clinical settings. First developed and evaluated in the YNHH Emergency Department (ED) [63–65], the purpose of the BNI is to assist patients in recognizing and changing levels of alcohol consumption that pose health risks. It relies on strategies from motivational interviewing (MI) and the stages of change model [66]. The main goals are to: (1) decrease ambivalence about reducing alcohol use; and (2) negotiate strategies for change. During the 15–20 min BNI, the HPA will: (1) *Raise the subject* of alcohol use; (2) *Provide feedback*: review the patient’s alcohol consumption, make a connection to the patient’s medical condition and reason for hospitalization; review guidelines for lower risk alcohol use; (3) *Enhance motivation*: via a readiness change ruler, which can assist in developing discrepancy; and (4) *Negotiate and Advise*: negotiate goal, provide feedback, ask patient to complete drinking agreement; summarize and arrange follow-up. Participants are provided a pamphlet regarding the impact of AUD on health and potential treatment resources (Additional files: 1, 2). The BNI session follows a structured encounter form and is digitally recorded for fidelity monitoring purposes. Consistent with our prior approaches [67, 68], the ED-based BNI manual was adapted by our team for relevance to racially and ethnically diverse hospitalized patients with AUD. All participants will be referred for formal AUD treatment per American Society of Addiction Medicine (ASAM) criteria [57] prior to discharge for ongoing AUD treatment. For this trial, we considered this the “control” condition given that this is consistent with standard of care [69] and we anticipate our approach guided by an interdisciplinary team with diverse perspectives and expertise will bolster this standard.

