#### Statistical analyses

##### Primary and secondary outcomes

The primary objective of this analysis will be to determine if the proportion of participants with formal AUD treatment engagement (yes/no) at 34 days post-discharge differs among those randomized to BNI alone, BNI + MAUD, and BNI + MAUD + CBT4CBT in this diverse sample. The primary outcome (1a) of AUD treatment engagement is binary and we will use logistic regression with two planned contrasts to evaluate statistical significance of the differences in proportion of formal AUD treatment engagement (as verified through electronic medical record and/or contact with treatment facility). This statistical model will also be used to assess efficacy of study interventions on AUD treatment engagement at 90-days following randomization (1a). Secondary outcomes (1b) will include change in the self-reported percentage of heavy drinking days (PHDD) by month from the 30-day period prior to hospitalization (baseline) to the 34- and 90-day post-discharge timepoint, which will be evaluated with random effects regression statistical models. These models have several advantages in follow-up data from clinical trials of individuals who use substances, as they are less vulnerable than traditional MANOVA approaches to missing data [85, 86]. An additional secondary outcome will include change in biomarker PEth, which as a continuous outcome will be evaluated with a similar statistical approach. Given limited data on factors impacting PEth levels among hospitalized patients [87] and building from our own experiences [88], we will also evaluate the correlation between baseline self-reported alcohol use (in the 30-day period prior to hospitalization) and PEth levels (e.g., liver disease, hemoglobin [38]), factors associated with PEth levels adjusting for baseline self-reported alcohol use, and factors impacting change in PEth from baseline to follow-up. Exploratory outcomes of healthcare utilization, including rates and costs of emergency department visits and hospital readmissions during the 34- and 90-day post-discharge period will be evaluated with mixed model ANOVAs. Analysis of treatment effects on primary, secondary, and exploratory outcomes will include the following contrasts: *H1:* BNI + MAUD > BNI; BNI + MAUD + CBT4CBT > BNI + MAUD or BNI.

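### Aim 3 puts its statistical cost-effectiveness comparison on arm-wise effectiveness/cost ratios, which do not measure what each added component buys; the planned ICER should carry the inference.

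*Protocol article*

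**What the plan says.** All of this is in the protocol article.

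- **Ratios.** Implementation-focused process evaluation: "Average and median effectiveness/cost will be compared statistically for each condition with individual-level effectiveness and costs". The example given there is "change in PHDD per $100 of resources consumed by intervention". The Abstract also names effectiveness/cost ratios as the cost-effectiveness indices to be compared between conditions.
- **Numerator.** Primary and secondary outcomes defines the PHDD outcome as "change in the self-reported percentage of heavy drinking days (PHDD) by month from the 30-day period prior to hospitalization (baseline" to follow-up, that is, within-patient change.
- **Cost per engaged patient.** Implementation-focused process evaluation: "Intervention-level cost per engaged patient will be calculated, along with increments in this cost as successive interventions are added".
- **ICERs.** Study aims and hypotheses lists individual-level comparisons "as well as intervention-level indices of incremental cost-effectiveness ratios (ICERs". The methods section does not use the term or give a formula.
- **Net benefit.** The methods section also plans graphical and statistical analysis of "individual-level net benefit (i.e., reduction following intervention in costs of ED and readmission minus costs of intervention".
- **Nesting.** The BNI section: "All participants receive the BNI with referral to aftercare AUD treatment". The other two arms add components to it.

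**The concern.** With nested arms, the economic question is whether facilitated MAUD, and then CBT4CBT, is worth its extra cost. That needs the difference in effect set against the difference in cost between adjacent arms. An arm-wise ratio of each patient's own change to own cost answers another question: how much change accompanied each $100 spent, whatever caused the change. Three features follow.

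1. Change that BNI alone would produce stays in the numerator of every arm, while the denominator grows with each component.
2. For patients who worsen, a higher cost makes the ratio look better.
3. The ranking of arms takes no account of what a unit of effect is worth.

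The increment in cost per engaged patient has its own difficulty. Read literally it is a difference between two averages, which is not the cost of engaging one more patient. A reader who took it as that cost would think the added component cheaper than it is.

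The Discussion offers the cost results as guidance for other health systems, so a test pointing the wrong way could mislead the intended users.

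**Working it through.** The article states no cost, ratio or ICER, so there is no figure to reproduce. Engagement rates come from Justification of sample size: 40% under BNI, and 55% or 60% after increases of 15 or 20 (read as percentage points). Costs are assumptions, shown over a range.

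**1. When the engagement ratio favours BNI.** With engaged proportion p and mean cost C, the arm-level ratio is p/C. BNI (arm 0) is ahead of the richer arm (arm 1) when p0/C0 > p1/C1, that is, when C1/C0 > p1/p0. The threshold is 0.55/0.40 = 1.375, or 0.60/0.40 = 1.5 in the second scenario. Below it the richer arm is ahead: at 1.2 times the cost, 0.458 v 0.400 engaged per 100 units.

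**2. Increment in average cost against ICER.** Let D = (C1 − C0)/(p1 − p0). Substituting C1 = C0 + D(p1 − p0):

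C1/p1 − C0/p0 = D(1 − p0/p1) − C0(p1 − p0)/(p0·p1)

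If C1 ≥ C0 > 0 and p1 > p0 > 0, the first term is at most D and a positive amount is then subtracted. The increment is therefore always below D, whatever the costs. At 40% v 55% with BNI cost set to 100 units:

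| Cost multiple | Increment in average cost | ICER |
|---|---|---|
| 1.1 | −50 | 67 |
| 1.2 | −32 | 133 |
| 1.5 | 23 | 333 |
| 2 | 114 | 667 |
| 3 | 295 | 1333 |
| 5 | 659 | 2667 |

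From 1.5 to 5 times the cost, the ICER is about 15 to 4 times the increment. At 1.1 and 1.2 the increment is negative although each extra engaged patient costs money. In dollars, with assumed costs of $50 and $150: 150/0.55 − 50/0.40 = 273 − 125 = $148, against 100/0.15 = $667.

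**3. Individual PHDD ratios.** Simulation with 150 per arm, 4000 runs and a two-sided Welch test at 0.05. Assumed: mean falls of 25 (BNI) v 35 points, SD 30, and log-normal costs with CV 0.5, independent of effect. A direct test of the 10-point difference succeeds in about 82% of runs.

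| Cost multiple | Mean ratio, BNI v richer arm (points per 100 units) | Ratio test significantly favours BNI |
|---|---|---|
| 1.2 | 31.2 v 36.5 | 0.1% |
| 1.5 | 31.3 v 29.2 | 7% |
| 2 | 31.2 v 21.8 | 62% |
| 3 | 31.3 v 14.6 | over 99% |

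The break-even multiple is 35/25 = 1.4. At twice the cost the ICER is 100/10 = 10 units per point. Anyone who values a point at more than 10 units should prefer the richer arm, yet the ratio puts BNI first whatever a point is worth. With falls of 10 v 35 points at twice the cost, the richer arm has the better ratio (21.9 v 12.5).

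**4. Patients who worsen.** A 10-point rise scores −10/50 × 100 = −20 per $100 at a cost of $50, but −10/150 × 100 = −6.7 at $150. The same harm looks milder because more was spent.

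**5. Mean against median.** If yes/no engagement is the effect, the median individual ratio is 0 when 40% engage and positive when 55% do, whatever the cost. At twice the cost the arm-level ratio favours BNI (0.400 v 0.275 per 100 units) while the median favours the richer arm.

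**The case against.** **The right measure is already planned.** Study aims and hypotheses commits Aim 3 to ICERs, and the methods section adds individual net benefit and other indices of cost and effect. This stands in part. It rules out the inference, which a reader might draw, that Aim 3 cannot say whether MAUD or CBT4CBT is worth adding. But the ICERs are an additional intervention-level item, while the cost-effectiveness testing described in the methods is attached to the ratios. The net benefit is a difference and escapes the ratio problems, but it counts only ED and readmission savings less intervention cost. Engagement and PHDD have no value in it.

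**The tilt depends on costs nobody has stated.** This stands. A reader might infer that the ratios favour the cheapest arm almost by construction, or that BNI would rank first. The article does not support that: costs are not given, the richer arm is ahead below the break-even multiple, and the median engagement ratio can point the other way. Facilitated MAUD as described is counselling within the BNI, a pamphlet and a record note, with prescribing left to the primary team, so its cost multiple may be modest.

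**The increments sentence may be loose wording for the ICER.** Possible, and an article may leave formulas to fuller documents. The literal reading is nevertheless a different quantity, and the two sections should agree.

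**The ratio approach is deliberate and referenced, and Aim 3 does not touch the primary inference.** Both are true. Neither makes the ratio answer the incremental question.

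**Conclusion.** The point holds in limited form. The methods text directs its statistical cost-effectiveness comparison at ratios that can rank the arms opposite to the value of the added component. It does not make the ICER promised in the aims the inferential comparison.

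Two results need no assumed costs. The ratio favours BNI exactly when cost rises proportionally more than effect (above 1.375-fold for engagement at 40% v 55%, or 1.5-fold at 40% v 60%). The literal increment in cost per engaged patient is always below the cost of an additional one, provided the richer arm costs at least as much and engages more patients.

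The dollar figures and simulated percentages rest on the assumed costs, PHDD changes and spread. They show what can happen, not what will. The primary and alcohol-use analyses are unaffected.

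**What to change.** In Implementation-focused process evaluation:

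- Make the between-arm incremental analysis the main cost-effectiveness comparison for the two adjacent contrasts: BNI + MAUD v BNI, and BNI + MAUD + CBT4CBT v BNI + MAUD. Report the ICER from the aims as difference in mean cost over difference in engagement proportion, or in mean PHDD reduction.
- Express uncertainty through incremental net benefit, λ × (difference in effect) − (difference in cost), over a stated range of λ. Regressing each patient's λ × effect − cost on arm gives this with confidence intervals.
- Replace the wording about increments in cost per engaged patient with that ICER, so that methods and aims agree.
- Keep the individual ratios and scattergrams as description, without significance tests.

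The individual costs and effects are already to be collected, so the cost is a change of wording and modest programming. The one new commitment is a range for λ, since the article puts no value on an engaged patient or a PHDD point.
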